### Participants and study settings

Participants will be recruited from two private spine clinics with referrals from the regions, in Sweden: Capio Spine Center Göteborg and Ryggkirurgiskt centrum (RKC), Sophiahemmet, Stockholm. Inclusion criteria: (i) patients planned for decompression surgery (without concomitant fusion) due to lumbar central spinal stenosis; (ii) patients > 18 years of age. Exclusion criteria: (i) patients with malignancy, severe neurological -or rheumatological disease, idiopathic scoliosis, or isthmic spondylolisthesis; (ii) persons unable to understand written information and communicate in Swedish; and (iii) patients with untreated/unstable heart disease that prohibits physical capacity tests. For patients meeting the inclusion criteria, the following screening criteria should also be fulfilled: (i) low level of physical activity (i.e. persons who do not meet WHO’s physical activity recommendations of a weekly minimum of 150 min of physical activity of moderate intensity), and (ii) higher levels of fear of movement or pain catastrophizing, equivalent with scores ≥ 37 on the Tampa Scale of Kinesiophobia (TSK) [33] and ≥ 30 on the Pain Catastrophizing Scale (PCS) [34].

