### Procedure

At baseline (approximately 2 weeks preoperatively) and follow-up (11–12 weeks postoperatively), physical activity, physical capacity and PROMs will be assessed. For physical activity, once the patient has agreed to participate in the study, the study coordinator will mail an accelerometer (ActiGraph GT3X + ; ActiGraph, Pensacola, FL, USA) and written user information to the participant for a 7-day assessment. Thereafter, an independent observer will collect demographic/clinical data and conduct physical capacity tests via video. In case of adverse events during video assessments, the independent observer has been instructed to contact medical care immediately if the patient becomes acutely ill or guide the patient to seek medical care if more of a subacute nature. The patient will fill out the PROMs through a secure digital platform (the application BASS, Karolinska Institutet, Stockholm, Sweden). During the intervention, the participants will also fill out weekly repeated measurements in BASS. These weekly measures will include twelve one-item questions addressing physical activity levels, fear of movement, catastrophizing, self-efficacy, and steps per day. Reminders will be sent out automatically via text message if the participant has forgotten to fill in a questionnaire in BASS. At the end of the study, a telephone-based semistructured interview, with all intervention participants, regarding feasibility aspects and participation will be conducted by the study coordinator. Feasibility data will be collected continuously during and at the end of the study period (see Fig. 3).

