#### Physical activity level

Objectively measured by a digital triaxial accelerometer (ActiGraph) via the variables, steps per day, time spent in light physical activity, moderate to vigorous physical activity (MVPA), and time spent sedentary [54].Self-reported physical activity with a two-item questionnaire from the National Board of Health and Welfare in Sweden [55].

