#### Process and resource feasibility

Process feasibility [68] will be administered by the following variables: recruitment, intervention use, and acceptability. Recruitment aspects include the percentage of patients eligible after the screening procedure, as well as the reasons for declining participation or dropping out of the study. Patients who withdraw from the study will also be asked if data collected up until the time point of the withdrawal can be used in the study. Intervention use will be calculated as the ratio of the number of completed treatment sessions versus the number of planned sessions. Acceptability with the digital format and intervention will be evaluated using a semistructured interview at the end of the intervention where all intervention participants will be asked about their experience. The Study PT will answer a questionnaire with specific questions about their experience with the intervention. Furthermore, all study participants and assessors will be asked to complete study-specific questionnaires about their thoughts on the digital data collection format (including both PROMs and physical capacity tests) and using the accelerometer. The self-reported physical activity level at screening will be compared with accelerometer data at baseline to evaluate the chosen questionnaire’s ability to detect patients with a low level of physical activity. Treatment safety will be addressed by the type and frequency of possible adverse events during the intervention collected by the Study PT after each session.

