### Statistical methods

Feasibility data will be analysed and reported descriptively. Demographic and clinical data will most likely be reported using a nonparametric approach, such as proportions and medians together with adequate approaches for describing variability, such as interquartile ranges or 95% confidence intervals. Similarly, we will also use nonparametric inferential tests for tentative analyses of efficacy and changes in outcomes within and between groups. In addition, data from the repeated measures will be plotted and analysed visually regarding changes in slope, medians, variability and regarding systematic patterns in these factors within and across participants [70]. The significance level will be set at a *p* value of 0.05. Numeric data will be analysed using the latest versions of IBM SPSS Statistics and/or RStudio. Accelerometer data will be analysed using ActiLife version 6 software. A wear time of a minimum of 10 h per day for at least 4 days will be considered valid [71]. Physical activity data will be reported as average steps per day, as well as minutes per week in each intensity category. We will calculate the proportions of patients who reached < 5000 steps per day (sedentary lifestyle), 5000–7499 steps per day (low active), 7500–9999 (somewhat active), and ≥ 10,000–12,499 steps per day (active) [72]. The proportion of participants in each physical activity level category as well as the proportion reaching the recommendations for health-promoting physical activity made by the WHO will be presented numerically and graphically. Data from the individual telephone interviews with the intervention participants will be transcribed verbatim. The text material will be analysed using inductive content analysis with a descriptive manifest approach.

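### Sedentary and light activity reported as minutes per week rise with hours of accelerometer wear, so changes and arm differences can reflect wear time alone

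*Protocol article*

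**What the plan says.** The Procedure section plans accelerometer wear at baseline and follow-up, with a device posted to the patient together with "written user information to the participant for a 7-day assessment". Under Physical activity level, the accelerometer variables are steps per day, "time spent in light physical activity, moderate to vigorous physical activity (MVPA), and time spent sedentary".

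The Statistical methods section then fixes two things:

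- The validity rule: "A wear time of a minimum of 10 h per day for at least 4 days will be considered valid".
- The reporting unit: "Physical activity data will be reported as average steps per day, as well as minutes per week in each intensity category".

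The same section announces nonparametric tests within and between groups as tentative analyses of efficacy. It also says that "the proportion reaching the recommendations for health-promoting physical activity made by the WHO will be presented numerically and graphically", without naming the data source. The WHO threshold appears in the screening criteria as "weekly minimum of 150 min of physical activity of moderate intensity".

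Under Process and resource feasibility, the accelerometer has a second use: "The self-reported physical activity level at screening will be compared with accelerometer data at baseline". This serves research question 7, on whether the screening questionnaire detects low activity.

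**The concern.** Every worn minute is assigned to an intensity category. The longer the device is worn, the more minutes there are to assign, and in patients selected for low activity most of them will be sedentary or light. A weekly total in minutes therefore mixes two quantities: how the patient behaved and how long the device was on. The validity rule sets a floor of 10 h per day and no common wear time, so patients with very different wear are pooled as equally valid.

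Wear could change between the preoperative and postoperative weeks. It could also differ between an arm coached to self-monitor steps and an arm receiving usual physical therapy. The article gives no evidence that it will, but the stated unit offers no protection if it does. At stake is whether a shift in sedentary or light time, read as tentative efficacy information under research question 1, is behaviour or wear.

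**Working it through.** The article gives no figure of its own on this point, so there is nothing to reproduce. The check is arithmetic on the stated rule.

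**Inputs from the article:** at least 10 h per day on at least 4 days; a 7-day assessment; minutes per week as the unit.

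**Assumptions, not in the article:** wear of up to 15 or 16 h per day; 65 to 70% of wear sedentary; 32% of wear light (paired with the 65%). Identical behaviour means that these shares do not change with hours worn.

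**Step 1. Range of valid wear.** Minimum: 4 × 10 × 60 = 2,400 min. Upper case: 7 × 16 × 60 = 6,720 min. The ratio is 6,720 / 2,400 = 2.8, made up of 7/4 = 1.75 from days and 16/10 = 1.6 from hours.

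**Step 2. Remove the day effect.** Take the reading most favourable to the plan: weekly minutes = share × hours per day × 60 × 7. The number of valid days drops out. Hours per day do not.

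| Assumed share of wear | 10 h/day | 15 h/day | 16 h/day |
|---|---|---|---|
| Sedentary, 65% | 2,730 | 4,095 | 4,368 |
| Sedentary, 70% | 2,940 | 4,410 | 4,704 |
| Light, 32% | 1,344 | 2,016 | 2,150 |

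The ratio to the 10 h column is 15/10 = 1.5 or 16/10 = 1.6 in every row. It does not depend on the assumed share.

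**Step 3. A smaller contrast.** One extra hour of wear per day adds 0.65 × 60 × 7 = 273 min per week of sedentary time (294 at 70%) and 0.32 × 60 × 7 = 134 min of light time.

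**Step 4. As a share of wear.** Sedentary time is 65% at 10 h and 65% at 16 h. The artefact disappears.

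**Step 5. MVPA.** With 25 min of MVPA per valid day, the mean times 7 is 175 min per week whether 4 or 7 days are valid. Hours worn matter here only if MVPA takes place while the device is off. In the extreme case where MVPA is proportional to wear, at 25 min per 14 h, the weekly figure is 25 × 10/14 × 7 = 125 min at 10 h and 25 × 16/14 × 7 = 200 min at 16 h.

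**The case against.** A reader might infer that minutes are simply summed over the recorded days. Then 150 min per week would need 150/7 = 21.4 min per day with 7 valid days but 150/4 = 37.5 with 4, and a patient at 25 min per day would score 175 or 100 and be classed differently. The article does not support this. It never says that minutes are summed unscaled. Minutes per week reads naturally as a weekly rate, in line with the daily average used for steps in the same sentence. Nor does it say that the WHO proportion comes from the accelerometer; it could come from the two-item questionnaire, where wear is irrelevant. Misclassification against the WHO threshold is therefore not shown.

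It can also be said that wear-time processing is detail an article leaves to the full protocol or analysis plan. That is fair for the scaling to 7 days, which is why it is treated here only as a clarification. It does not dispose of the main point, because the article itself states the unit, and that unit depends on wear under either reading.

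Two further objections stand in part. The contrast of 10 with 15 or 16 h compares two individuals towards the ends of an assumed range; it does not estimate a bias between arms, and no passage shows differential wear. The consequence is also limited: the Background makes steps per day the main focus, research question 1 does not name sedentary or light time, and no decision rule in the article depends on them.

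**Conclusion.** The point holds for sedentary and light time. Reported in minutes per week, both scale with hours worn even after conversion to 7 days: 1.5- to 1.6-fold for 10 against 15 to 16 h per day, or about 273 to 294 min of sedentary time per week for each extra hour of daily wear. The fold figures assume the upper wear values and a composition of wear that does not change with its length. The minute figures also assume the 65 to 70% sedentary share. The actual wear in this trial, and any difference by arm or time point, cannot be known from the article.

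For MVPA and the 150-minute threshold there is no demonstrated error, only scaling that is worth stating. It matters a little more for research question 7, where the accelerometer is the yardstick for the screening questionnaire. Overall this is a modest but worthwhile correction in a 30-patient feasibility study with tentative efficacy analyses.

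**What to change.** In Statistical methods:

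1. Compute time in each intensity category as the mean per valid day.
2. Report sedentary and light time as a percentage of wear time and use that measure for comparisons within and between groups. Minutes may be kept alongside.
3. Show the number of valid days and mean wear hours by arm at baseline and follow-up, next to steps per day.
4. For any accelerometer comparison with 150 min per week, including the check of the screening questionnaire, state that MVPA is the mean per valid day times 7. Name the data source of the WHO proportion.

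A percentage removes the mechanical dependence on hours worn. It does not correct for unworn hours that differ in kind from worn ones, which is why the wear figures should be shown as well. The cost is a few lines of analysis wording and one extra table row. No new data are needed, since daily wear must already be derived to apply the validity rule.

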## Discussion

Persons with physical activity levels below global recommendations have a substantially increased risk of developing poor overall health in comparison to those who are sufficiently active [38]. Therefore, increasing health behaviours such as physical activity is a public health priority. Patients undergoing lumbar spine surgery are less likely to meet recommendations for healthy physical activity at long-term follow-up after surgery compared to population norms [4]. Moreover, higher anxiety and fear-avoidance beliefs about pain are associated with lower physical activity (measured as step counts) in LSS patients specifically [16]. To our knowledge, this study will be the first of its kind to evaluate the feasibility of a person-centred and digital health-promoting intervention aiming to increase physical activity for risk patients undergoing decompression surgery for LSS.

In addition, Get Back aims to move away from a one size fits all approach to a person-centred approach in terms of both treatment and treatment outcomes. Given the multidimensional complexity of physical functioning in LSS, Get Back_feasibility_ will use a combination of PROMs, physical capacity tests, and accelerometer data to capture a comprehensive picture of patient functioning following surgery.

Based on the results of this feasibility study, the intervention will be refined by revisiting both the content and study procedure prior to the start of a randomized controlled trial evaluating the effect of the intervention. In the long term, if the intervention shows similar or improved outcome effects compared to those in the control group (receiving usual physical therapy), this could bring important knowledge to the field of lumbar spine rehabilitation. Furthermore, the intervention could facilitate equal rehabilitation by supporting the use of digital solutions that can benefit patients with long travel distances to rehabilitation centres.

## Trial status

Start of study enrolment April 17th, 2023.

## Data Availability

Not applicable, as this is a study protocol which does not contain any data. Additional data management information: Please see Additional file 2.

## Abbreviations

LSS: Lumbar spinal stenosis
CBT: Cognitive behavioural therapy
PROM: Patient-reported outcome measure
WHO: World Health Organization
TSK: Tampa Scale of Kinesiophobia
PCS: Pain Catastrophizing Scale
PT: Physical therapist
BCT: Behaviour Change Technique
MVPA: Moderate to vigorous physical activity
